## Abstract

**Background:**

This protocol was developed to describe the design of a randomised controlled trial that will examine the clinical efficacy of a 4-week comparison of high-intensity vs. low-intensity physical training for people suffering from anxiety. The hypothesis is that the high-intensity group will have greater benefit in terms of reduced anxiety symptoms, improved physical health (blood pressure) and better adherence.

**Methods:**

Thirty adults aged 18 to 70 years diagnosed with an anxiety disorder will be recruited for this study. Participants will be randomised into an intervention group (high-intensity training) and a control group (low-intensity training). Randomisation will be performed using counterbalanced block randomisation in a 1:1 ratio, stratified by sex. Both groups will perform 4 weeks of twice-weekly training supervised by an exercise physiologist. The primary outcome will be the total score on the Hospital Anxiety and Depression Scale (HADS) and the total score on the Beck Anxiety Inventory (BAI). The secondary outcomes include blood-pressure changes and adherence. Evaluations will be performed at baseline and following 4 weeks of the interventions, and 6 months after the termination of the intervention period (secondary endpoint).

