## Outcomes

### Primary outcome measures

The primary outcome measure will be the degree of anxiety symptoms measured by the Hospital Anxiety and Depression Scale (HADS) [25] and the Beck Anxiety Inventory (BAI) [24] prior to the first (pre) and after the last (post) training session is completed.

The HADS is a questionnaire that measures self-report levels of some symptoms of anxiety and depression [25]. The instrument consists of 14 questions (items), of which 7 are related to anxiety symptoms (HADS-A) and 7 to depression symptoms (HADS-D). Each item is rated from 0 to 3, which gives a range of scoring from 0 to 42, with a score ranging between 0 and 21 for the anxiety (HADS-A) and depression (HADS-D) subscales. The HADS is one of the most commonly used self-report instruments for measuring anxiety and depression [29] and has demonstrated good reliability and validity and has sound psychometric properties [29]. A previous study found a minimal clinically important difference (MCID) between 0.5 and 5.57 for the HADS-D, and between 0.81 and 5.21 for HADS-A [30]. We will calculate total HADS scores and subscores for anxiety symptoms and depressive symptoms, respectively.

The Beck Anxiety Inventory (BAI) [24] is a questionnaire that measures self-report levels of some symptoms of anxiety. The instrument consists of 21 questions (items), and each item is rated from 0 to 3, which gives a range of scoring from 0 to 63, a higher score indicating increased symptoms. The BAI measures anxiety symptoms including muscle tension, dizziness, racing heart, nervousness, fear of dying, abdominal discomfort, face flushing, sweating, light-headedness, fear of the worst happening and a feeling of choking. The BAI is one of the most commonly used self-report instruments for measuring anxiety [31] and has demonstrated good reliability and validity and has sound psychometric properties [32]. We will calculate total BAI scores.

Both the Hospital Anxiety and Depression Scale (HADS) and the Beck Anxiety Inventory (BAI) will be applied. HADS allows comparability with both psychiatric and somatic populations, while BAI provides a more detailed assessment of somatic anxiety symptoms. Using both HADS and BAI increases sensitivity and also validity in assessing anxiety.

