### Statistical analysis

Data management and analyses are performed using SPSS 30 (SPSS Inc., Chicago, IL, USA). Data will be analysed using descriptive and inferential statistics. Continuous variables are presented with mean ± SD and 95% CIs.

The effect of the intervention will be assessed by examining change scores on the BAI and HADS (primary outcomes) and blood pressure and EKG (secondary outcomes). Changes from baseline to post-tests (immediately, after four weeks, and after three months) will be analysed.

Single measures (e.g. baseline data) will be analysed using ANOVA or linear regression, provided the statistical assumptions for linear models are met. Variables will be assessed for normality through visual inspection of histograms and Q-Q plots, along with a formal test for normality (Shapiro-Wilk test). If the assumption of normality is violated, non-parametric tests will be applied. ANOVA with repeated measures will be used to analyse changes in quantitative data (change scores) and to compare the two groups.

Missing data will be handled using linear mixed-model analyses, which provide unbiased estimates under the assumption that data are missing at random and allow inclusion of all available observations. Furthermore, multiple imputation will be applied as a sensitivity analysis to assess the robustness of the results to potential missingness.

We will also use Bonferroni corrected post hoc comparisons when performing multiple comparisons, ensuring that the overall significance level remains accurate. Additionally, effect sizes are estimated based on Cohen’s *d* (0.2 = small effect, 0.5 = medium effect, and 0.8 = large effect).

Participants with mild-to-moderate depressive symptoms will be eligible for inclusion, as anxiety and depression frequently co-occur in clinical populations. Due to our limited sample size, formal subgroup analyses based on depression status will not be conducted. Instead, the baseline depressive symptom scores (HADS-D) will be entered as a covariate in the statistical models to adjust for their potential influence on anxiety outcomes.

Age will be included as a covariate in all primary and secondary analyses. In addition, exploratory subgroup analyses will be performed by age group (< 40 years vs ≥ 40 years).

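### The abstract makes the HADS total a primary outcome although half of it is depression and the hypothesis is about anxiety; no section names HADS-A as the primary score

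*Protocol article*

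**What the plan says.** - **Abstract, Methods.** This is the only place that says which HADS score is primary: "The primary outcome will be the total score on the Hospital Anxiety and Depression Scale (HADS"), named together with the BAI total.
- **Primary outcome measures.** The body describes a construct, not a score: "The primary outcome measure will be the degree of anxiety symptoms measured by the Hospital Anxiety and Depression Scale (HADS") and the BAI. It then gives the composition of the HADS, "of which 7 are related to anxiety symptoms (HADS-A) and 7 to depression symptoms (HADS-D"), and its range, "which gives a range of scoring from 0 to 42, with a score ranging between 0 and 21 for the anxiety (HADS-A) and depression (HADS-D)". On scoring it says: "We will calculate total HADS scores and subscores for anxiety symptoms and depressive symptoms, respectively". None of the three scores is called primary here.
- **Hypotheses/aims and benefits.** The first hypothesis is a larger reduction in anxiety with high-intensity exercise. No hypothesis concerns depression.
- **Statistical analysis.** The primary outcomes are listed as BAI and HADS, with no HADS score named. The section adds that "the baseline depressive symptom scores (HADS-D) will be entered as a covariate in the statistical models", to allow for the influence of depression on anxiety outcomes.
- **Sample size calculation.** The calculation uses the BAI alone.

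**The concern.** The only HADS score explicitly named as primary is one in which anxiety and depression count equally. This opens two routes to a misleading result. A difference carried by the depression items could be reported as an anxiety benefit. Conversely, a real anxiety effect could be diluted if depression moves little.

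The first route is plausible on the article's own account. The inclusion criteria expect comorbid depressive symptoms, and the Background cites evidence that exercise reduces depression as well as anxiety.

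The body does not correct the abstract. It leaves three HADS scores available, so the choice among them could be made after the results are known.

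**Working it through.** **1. Composition of the total (Primary outcome measures).** Depression share: 7/14 items = 50%, and 21/42 points = 50%.

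**2. The plan's own sample size.** Inputs from the Sample size calculation: BAI 14 against 22, so a difference of 8; SD 7; two-sided alpha 0.05; power 80%.

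- d = 8/7 = 1.143.
- Normal approximation: n per arm = 2 × [7 × (1.960 + 0.842)/8]² = 12.02. This matches the stated 12 per arm, 24 in total.
- Attrition of 20%: 24/0.80 = 30, as stated.
- With the noncentral t distribution, power at 12 per arm is 76.3%. The same method is used below.

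The figure reproduces, but it says nothing about the HADS.

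**3. Illustration for the HADS total.** The article gives no HADS effect, SD or correlation between subscales. Everything in this step is therefore assumed: HADS-A carries the BAI effect (d_A = 1.143), the subscale SDs are equal, the correlation r is 0.3 to 0.7, and the effect on HADS-D is a fraction k of that on HADS-A.

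With common SD s, the total has variance 2s²(1 + r), so

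d_total = d_A(1 + k) / √[2(1 + r)].

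At r = 0.5 the divisor is √3 = 1.732:

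- k = 0: 1.143/1.732 = 0.660
- k = 0.5: 1.714/1.732 = 0.990
- k = 1: 2.286/1.732 = 1.320

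Power on the total, 12 per arm, two-sided 0.05, noncentral t:

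| HADS-D effect | r = 0.3 | r = 0.5 | r = 0.7 |
|---|---|---|---|
| none (k = 0) | 38% | 34% | 31% |
| half (k = 0.5) | 70% | 64% | 59% |
| equal (k = 1) | 91% | 87% | 83% |

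HADS-A alone: 76%.

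**4. Break-even.** The total matches HADS-A when 1 + k = √[2(1 + r)]. That gives k = 0.61 at r = 0.3, 0.73 at r = 0.5 and 0.84 at r = 0.7. Below these values the total loses power; above them it gains.

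**5. The mirror case.** The formula is symmetric in the two subscales. Under the same assumptions with r = 0.5, an effect of 1.143 on depression alone, with no anxiety effect, would make the total significant 34% of the time.

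**The case against.** The case on the other side has several parts.

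- **The total is called primary only in the abstract.** The body speaks of anxiety symptoms and plans the HADS-A score, which suggests an anxiety score may have been meant. This stands: the defect is partly a mismatch between abstract and body. But no section names HADS-A as primary, so the abstract is the only explicit statement.
- **The BAI total is anxiety-specific, is also primary and carries the sample size.** This stands and limits the harm. It does not remove it, because the article does not rank the two outcomes and a result on the HADS total could be presented as a primary finding.
- **The planned subscores would reveal a depression-driven total.** True for a careful reader of the results, but the score named as primary would still be the total.
- **The total may gain power.** This stands: if depression responds equally, power on the total exceeds that on HADS-A. A reader might infer from the 34% alone that the choice must cost power; the article supplies no HADS inputs to support that.
- **Adjusting for baseline HADS-D is ordinary.** This stands. A reader might see a contradiction in adjusting for a component of the outcome, but baseline adjustment does not bias the randomised comparison. Equally, it does not take post-treatment change in HADS-D out of the total.
- **No minimal important difference is quoted for the total, only for the subscales.** This is minor, since none enters the sample size or a decision rule.

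**Conclusion.** The point holds as a mismatch between the named score and the hypothesis, together with a primary HADS score that the body never fixes. The HADS total is not a specific measure of anxiety. A reader might go further and conclude that it does not measure the anxiety hypothesis at all, or that the trial lacks an anxiety-specific primary outcome. The article supports neither: half the total is HADS-A, and the BAI total is primary too.

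The 50% depression share is exact. The power figures are not estimates for this trial. They rest on an effect size borrowed from the BAI, equal subscale SDs and an assumed correlation. Across correlations of 0.3 to 0.7 and a HADS-D effect from none to equal, power on the total runs from 31% to 91% for one and the same anxiety effect. What they show is that the result on this outcome would depend heavily on what depression does, in either direction. The stated sample size is unaffected.

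**What to change.** Name HADS-A (0 to 21) as the primary HADS score in the abstract, in Primary outcome measures and in Statistical analysis. Report HADS-D and the HADS total as secondary.

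Make the change before outcome data are analysed. Record it as an amendment through the ethics committee process described under Ethics and dissemination, and align the registry entry if it differs; that entry was not available for this review.

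No new data, participants or visits are needed, because all three scores are already planned. The costs are an amendment after recruitment has begun (January 2025, per Trial status) and possibly some power if depression also responds: in the illustration with r = 0.5 and an equal effect, 76% on HADS-A against 87% on the total.

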**Discussion:**

By investigating the clinical efficacy of a 4-week training intervention, we hope to provide applicable and generalisable knowledge about the efficacy of physical training for people suffering from anxiety disorders.

**Trial registration:**

Clinical Trials NCT06881758. Registered on 17 March 2025.

**Supplementary Information:**

The online version contains supplementary material available at 10.1186/s13063-026-09472-2.

## Background

Anxiety disorders are very common and may severely impact the quality of life of those affected [1]. It has been estimated that approximately 15% of the Norwegian population fulfil the diagnostic criteria for one or more anxiety disorders [2]. Based on extensive population surveys, as many as 33.7% of individuals will experience an anxiety disorder at some point in their lifetime [3].

In recent years, the potential benefits of physical exercise for mental health have been highlighted [4]. Physical activity is considered important for physical and mental health and is associated with a number of health benefits, including reduced blood pressure, greater heart capacity, less pain, improved insulin response, deeper sleep, stronger bones and improved metabolic health [5]. The Norwegian health authorities recommend physical activity as a central initiative for improving public health [6]. Further, the World Health Organization as well as national guidelines in Norway recommend at least 75 minutes of high-intensity exercise or 150 minutes of moderate-intensity exercise per week or a combination of these two [7, 8].

However, it is important to emphasise the well-documented effects of physical activity on mental health disorders [5]. Recent systematic reviews and meta-analyses have strengthened the evidence that physical activity has beneficial effects on depressive and anxiety symptoms [9–11]. Havnen and colleagues [12] found that more physically fit persons had a significantly lower consumption of anxiolytics and antidepressants. Further, physical activity may have a positive effect on people suffering from psychotic disorders [13].

Previous studies have found that endurance exercise at a low intensity may reduce depressive symptoms and anxiety symptoms [14]. An example of low intensity endurance training is prolonged exercise at approximately 60% of maximal heart rate. A potential mechanism for the effects of performing such exercise is the secretion of neurochemical substances (endorphins, serotonin and dopamine), which may have a positive effect on mood [15].

A recent meta-analysis concluded that performing endurance exercise at a high intensity may also reduce anxiety and depression [16]. High intensity exercise is shorter in duration (often shorter than 30 minutes) and with a heart rate between 85%–95% of maximal heart rate [17]. High intensity exercise is often performed in interval form, consisting of intermittent bouts of high and low intensity, a method which has been used frequently in research in recent years.

A so-called “4 × 4” interval session consisting of four minutes of high intensity divided into four bouts is a popular way of performing high-intensity exercise [18]. Recent studies have however found that the difference between performing 1 × 4 (i.e. one bout of four minutes) and 4 × 4 is small and non-significant in terms of training effect, measured by maximal oxygen uptake [19].

However, there has been some uncertainty regarding whether high-intensity exercise is superior to low-intensity exercise for mental health benefits [20]. A previous study found high-intensity exercise to have a significantly better effect on anxiety, compared to exercising at a lower intensity [21].

A more recent review by Singh and colleagues [14] also found high intensity exercise to have a better effect on mental health than lower intensity exercise. Additionally, the anxiety-suppressant and anti-depressant effect of high intensity exercise may come about rapidly, often after days or weeks [14]. An assumed mechanism is a larger secretion of signalling substances (serotonin and norepinephrine) following high intensity exercise compared to low intensity exercise [22]. Thus, it is important to examine the effect of high intensity exercise on mental health and whether a 1 × 4-interval protocol may be recommended for patients in mental health care.

An advantage of high intensity exercise is the shorter time required to complete a session compared to low intensity exercise. A high intensity exercise session is often completed in 20–30 minutes, with two sessions per week being sufficient. Thus, high intensity exercise is a time-efficient way of exercising, shown to have a higher compliance than exercising at lower intensities [23].

The shorter duration and higher perceived effectiveness of this type of training may further support continued exercise behaviour after the intervention period. High-intensity exercise may also lead to a greater reduction in blood pressure compared to low-intensity exercise [5, 14, 20], caused by improved autonomic regulation and cardiovascular adaptation. Changes in blood pressure may represent an important physiological marker of response.

Although the beneficial effects of exercise on anxiety are well documented, the optimal exercise intensity for reduction of anxiety is still unclear. This study therefore aims to provide new evidence on how exercise intensity influences both psychological and physiological outcomes. Together, these aspects represent the novel contribution of the present trial.

The main objective of this randomised controlled trial (RCT) is to evaluate the effectiveness of a four-week intervention involving high-intensity exercise, compared to low-intensity exercise. We hypothesise that the primary outcome measures (the Beck Anxiety Inventory [24] and the Hospital Anxiety and Depression Scale [25]) will show improvement as a result of the exercise. Furthermore, we also hypothesise that high-intensity exercise will lead to a significantly greater reduction in symptoms compared to low-intensity exercise.

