## Hypotheses/aims and benefits

The aim of the current RCT is to examine whether high-intensity exercise may reduce symptoms of anxiety in patients in mental health care.

We hypothesise that:The participants performing high-intensity exercise will have a significantly larger reduction in anxiety levels compared to the participants performing low-intensity exercise.The participants performing high intensity exercise will have a significantly higher degree of compliance (meaning that they will be able to complete the training autonomously three months after participating in the project) compared to the participants performing low intensity exercise.The participants performing high-intensity exercise will have a significantly larger improvement (i.e. reduction) in blood pressure than the participants performing low-intensity exercise.

The expected benefits for the participants are positive health effects, in terms of improved physical fitness and reduced psychological symptoms. Moreover, the participants will learn to use physical activity as a specific measure that they can utilise as a source of coping. Furthermore, knowledge about physical activity and mental health may be applicable in mental health care as part of a treatment plan.

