## Methods/design

This is a study protocol for a randomised controlled trial designed to test the effects of high intensity training compared to low intensity training on anxiety levels.

There will be a random 1:1 allocation into two groups. The two groups are high intensity exercise (1 × 4 minutes performed two times per week with a heart rate of 85–95% of maximal heart rate, corresponding to ≥ 16 on the 6–20 Borg scale) and low intensity exercise (45 minutes performed two times per week with a heart rate of approximately 60% of maximal heart rate, corresponding to 9–11 on the 6–20 Borg scale) [26]. The high intensity group will perform a 10-minute warm-up prior to the high-intensity bout, and a 5-minute cooldown. Due to the low intensity in the low intensity group, a warm-up is not considered necessary.

The total amount of training sessions for both groups will be eight. The high intensity exercise group will serve as the intervention group, while the low intensity exercise group will serve as an active control group.

The trial will be conducted in accordance with the Standard Protocol Items: Recommendations for Interventional Trials statement (SPIRIT) [27].

The trial has been approved by the Data Protection Officer at the University Hospital of North Norway and the Regional Committee on Health Research Ethics (approval number 714458) and registered at ClinicalTrials.gov (Trial registration number NCT06881758).

Participants will provide written informed consent before allocation to the two intervention groups, and they will be randomised into a high-intensity training group and a low-intensity training group, following baseline measures.

Randomisation will be performed using counterbalanced block randomisation in a 1:1 ratio, stratified by sex, to ensure an equal distribution of males and females across the study groups. Block sizes of four–six participants will be used. This will allow for a balanced representation of both genders in each condition. Randomisation will be conducted using a computer-generated random number sequence via the website https://www.randomizer.org/.

Outcomes will be measured immediately after inclusion (baseline), right after the very last exercise session, four weeks after the last exercise session (primary endpoint) and three months after the termination of the intervention period (secondary endpoint) (Fig. 1).

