The knowledge generated by this study may directly impact the evidence towards developing targeted interventions and the self-management of anxiety disorders, and the knowledge will be of importance in developing recommendations for the treatment of patients suffering from anxiety disorders. Should the treatment prove effective, this will be a simple, convenient and low-cost treatment option for many people.

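### The Background adds a hypothesis that anxiety improves because of exercise, which a trial with exercise in both arms cannot test

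*Protocol article*

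**What the plan says.** The last paragraph of the Background opens with a comparative main objective, high-intensity against low-intensity exercise over four weeks. It then gives two hypotheses. The first is that the primary outcome measures, BAI and HADS, "will show improvement as a result of the exercise". The second is set apart from it: "Furthermore, we also hypothesise that high-intensity exercise will lead to a significantly greater reduction in symptoms compared to low-intensity exercise".

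Hypotheses/aims and benefits words the aim without a comparator: "The aim of the current RCT is to examine whether high-intensity exercise may reduce symptoms of anxiety in patients in mental health care". The three hypotheses listed after it (anxiety, compliance, blood pressure) all compare the two groups.

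On design, Methods/design says "There will be a random 1:1 allocation into two groups". One group does high-intensity exercise, "while the low intensity exercise group will serve as an active control group". Both follow eight supervised treadmill sessions over four weeks. No group goes without exercise.

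Statistical analysis assesses the effect of the intervention through change scores: "Changes from baseline to post-tests (immediately, after four weeks, and after three months) will be analysed". The repeated-measures ANOVA is to serve both for the analysis of change and for the comparison of the two groups.

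**The concern.** The first hypothesis is causal, concerns both primary outcomes, and is stated in addition to the comparison of intensities. Randomisation in this trial identifies one contrast only, high against low intensity. For exercise against no exercise there is no randomised contrast, and no later analysis document can supply one.

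A fall in BAI or HADS from baseline could come from exercise. It could also come from regression to the mean (people come from a referral waiting list or answer media stories, and so may enter when symptoms are high), from the natural course, or from the attention that comes with eight supervised sessions, with self-report by participants who know their training. These are possibilities, not documented events, but the design can exclude none of them.

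The stake is what may be concluded if the arms improve equally. Read literally, the Background would count that result as a confirmed hypothesis, although it would show neither that intensity matters nor that exercise works.

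**Working it through.** **1. What the sample size supports.** Inputs from Sample size calculation: baseline BAI 30 in each group, expected post-treatment means 14 and 22, SD 7, two-sided alpha 0.05, power 80%.

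- Between-arm difference: 22 − 14 = 8.
- n per arm = 2 × (1.960 + 0.842)² × 7² / 8² = 2 × 7.849 × 49 / 64 = 12.02. The plan's 12 per group (24 in total) reproduces; power at 12 per arm is 79.9% by the normal approximation and 76.3% by the exact t-test.
- Attrition: 24 / (1 − 0.20) = 30, as stated.

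The stated size therefore belongs to the difference between arms and to nothing else.

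**2. What randomisation identifies.** The plan's figures imply falls of 30 − 14 = 16 and 30 − 22 = 8 points. Suppose a non-specific fall of m points is common to both arms. The parts due to exercise are then 16 − m and 8 − m, and their difference is 8 whatever m is. The trial can estimate that difference; it holds no information on m.

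**3. How easily a pre-post test turns out significant with no exercise effect.** Assumptions not in the document: exercise has zero effect, every participant has the same expected fall m, and the pre-post correlation r is 0.3, 0.5 or 0.7. From the document: SD 7 at each visit, 15 per group, 30 in total.

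- SD of change = 7 × √(2(1 − r)): 8.28, 7.00 and 5.42.
- Noncentrality = m / (SD of change / √n). Probability = chance that a noncentral t with n − 1 degrees of freedom exceeds the two-sided 5% critical value (2.045 for n = 30).
- Example, n = 30, m = 4: noncentrality 2.65, 3.13 and 4.04, giving 72%, 86% and 97%.

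| Assumed non-specific fall | One arm, n = 15 | Pooled, n = 24 | Pooled, n = 30 |
|---|---|---|---|
| 0 points | 2.5% | 2.5% | 2.5% |
| 2 points | 14–26% | 20–41% | 25–50% |
| 4 points | 41–76% | 62–93% | 72–97% |
| 8 points | 94% to >99% | >99% | >99% |

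Ranges run from r = 0.3 to r = 0.7. The column n = 24 shows the position after the expected 20% attrition. The paired t-test is a simple stand-in for the time effect of the planned ANOVA, which has more visits and covariates. The table shows scale; it does not predict the size of any non-specific fall.

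**The case against.** The strongest reply is that the trial is already comparative where it counts. The main objective in the Background, the three listed hypotheses, the opening of Methods/design and the sample size all set high against low intensity. The Background also treats the benefit of exercise as known and names the best intensity as the open question. On this view the disputed sentence is only a background expectation. Most of this stands: the main inference is not in danger. But the sentence is phrased as a hypothesis on the primary outcomes, it attributes the change to exercise, and the second hypothesis is introduced as a further one.

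Three stronger readings are tempting and are not supported.

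- A reader might infer that Statistical analysis plans to use the time effect as its test of efficacy. It does not say so. Change from baseline is an ordinary basis for comparing randomised arms, the ANOVA is also meant to compare the groups, and no success criterion is set on change over time. What can be said is that the section does not state which of its two uses decides the effect of the intervention.
- A reader might take the Discussion's closing remark, "Should the treatment prove effective, this will be a simple, convenient and low-cost treatment option for many people", as a planned within-arm claim. It is conditional and can equally mean that high intensity proves better than its comparator.
- A reader might add outpatient care begun during follow-up to the rival explanations. The article says that participation leaves waiting-list status unchanged, but it does not describe such care being started.

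It is also fair to say that neither the correlations nor the size of a non-specific fall can be taken from the document. With a fall of 2 points, the chance of a significant pre-post result in one arm of 15 is only 14% to 26%.

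**Conclusion.** The point holds in a limited form. The Background contains a causal hypothesis on the primary outcomes that this design cannot test, and the stated aim lacks its comparator. That much follows from the design alone and needs no numerical assumption. The illustration adds scale: with SD 7 and correlations of 0.3 to 0.7, a non-specific fall of 4 points, half the 8 points expected in the low-intensity arm, would make a pooled pre-post test on 30 participants significant in about 72% to 97% of trials, against 2.5% in that direction when nothing changes.

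It does not follow that the trial's main comparison is invalid or that its sample size is wrong; both rest on the between-arm difference and are untouched. The correction is worth making because it settles beforehand what may be claimed if both arms improve by the same amount.

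**What to change.** - **Background, last paragraph:** delete the first hypothesis, or label it a descriptive expectation that the trial does not test.
- **Hypotheses/aims and benefits:** add to the aim that the reduction is compared with low-intensity exercise.
- **Statistical analysis:** state that the effect of the intervention is judged by the between-arm difference in change; that within-arm and pooled change is descriptive, reported as a mean with 95% CI; and that finding no difference between arms would not show that either programme works.

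Arms, sample size, visits and data collection stay as they are. The cost is a narrower claim: the trial can speak on high against low intensity, not on exercise against none.
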